### Data analysis

We will analyze results primarily based on the principle of intention - to - treat (ITT) and subordinately based on the per - protocol (PP) principle. The ITT analysis will include any participants who are randomly allocated and have at least one EA or sham session. Missing values will be imputed by the last observation carried forward. The PP analysis will cover only the patients who have at least seven sessions of EA or sham treatments and have no medical diagnosis of UTI at the end point.

Continuous variables will be tested by the independent *t*-test if normality is obtained. Otherwise, the Mann-Whitney *U* test will be implemented. The categorical variables will be analyzed by the Pearson *χ*^2^ test or Fisher's exact test.

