### Dropout criteria

Patients will be removed from the study if they are unwilling to continue their participation in the study. Patients who fail or anticipate to fail in continuing at least seven sessions will be dropped from the study, too.

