### Blinding

The patients and outcome assessors will remain blinded during the study. Patients assigned to the sham group will undergo a similar treatment as those assigned to the EA group. Because we will use the Park-sham with non-penetrating acupuncture needles as control, electrostimulation will be turned on without conductance. In addition, we will use the same guide tubes used in the Park-sham acupuncture needles in the intervention group, too. Aside from the practitioners who will administer the EA or sham treatment, there will be an independent outcome assessor who will not be notified about the patients’ allocated arms.

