### Interventions

The EA and sham EA regimens are based on traditional Korean medicine. We referred to the textbook [14] and consulted acupuncture and stroke specialists.

The participants allocated to the EA group will receive five sessions per week of EA therapy for 2 weeks (ten sessions in total). After inserting needles (stainless steel, 0.25 mm in diameter and 4.0 mm in length; Dong Bang Acupuncture Inc., Republic of Korea) using the Park-sham guide tube on bilateral acupoints BL31, BL32, BL33, and BL34 (eight points in total) at 5–10 mm in depth, the *de qi* sensation is elicited. The locations of the acupoints according to the World Health Organization Standard Acupuncture Point Locations in the Western Pacific Region are illustrated in Fig. 2 [15]. *De qi* means an acupuncture needle sensation of soreness, tingling, fullness, ache, coolness, warmth, and heaviness, and a radiating sensation at and around the acupoints to the point of a threshold that elicits nerve impulse transmission to the cerebral cortex [16]. Then, electrostimulation will be administered for 20 minutes at a moderate frequency of 30 Hz (STN-111, Stratek, Republic of Korea).

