**Fig. 2 Fig2:**
[figure not shown]
The locations of acupoints BL31, BL32, BL33, and BL34. In the sacral region, BL31, BL32, BL33, and BL34 are located in the first, second, third, and fourth posterior sacral foramens, respectively. (World Health Organization Standard Acupuncture Point Locations in the Western Pacific Region)

We will use the Park-sham device in the control group. The non-penetrating needles of the sham acupuncture will be implemented on the same eight bilateral acupoints. The total number of sessions of sham EA is ten (five times per week for 2 weeks). The electrostimulation will also be administered for 20 minutes at moderate frequency (30 Hz; STN-111, Stratek, Republic of Korea), even though the stimulation will not be delivered through the skin because of the non-penetrating needle of sham device.

The use of conventional therapies will be allowed during the study for both groups. The conventional therapies consist of general supportive care, preventive or therapeutic management for medical/neurological complications, or drug treatments with antiplatelet agents, anticoagulants, or neuroprotectants. Moreover, stroke management with traditional herbal medications, acupuncture without electrostimulation, or rehabilitation for stroke complications will be permitted during the trial. However, any drugs, herbal medications, or rehabilitation that could affect UR will be prohibited. The study will conform to clinical practice guidelines for stroke management in Korea [17].

Practitioners who have over 1 year of clinical experience will perform the EA or sham EA treatments.

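### The primary set labelled intention-to-treat leaves out randomised participants who never start, and the decision to start is not shielded from knowledge of the arm

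*Protocol article*

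**What the plan says.** The Data analysis section of the protocol article ranks intention-to-treat first and per-protocol second. It then defines the first set: "The ITT analysis will include any participants who are randomly allocated and have at least one EA or sham session". Missing values are filled by last observation carried forward (LOCF). The only other set named, per-protocol, is narrower: it needs seven sessions and no urinary tract infection at the end. No section brings back participants who were randomised and not treated.

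Four other places bear on who can influence whether a first session takes place:

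- Blinding: "The patients and outcome assessors will remain blinded during the study". Treating practitioners are not on that list, and the next lines separate them from the assessor: "Aside from the practitioners who will administer the EA or sham treatment, there will be an independent outcome assessor who will not be notified".
- Interventions, EA arm: needles are inserted "at 5–10 mm in depth, the *de qi* sensation is elicited". Sham arm: "The non-penetrating needles of the sham acupuncture will be implemented on the same eight bilateral acupoints".
- Randomization: practitioners at each site contact the sub-investigators to obtain an allocation. The closing statement on blinding there covers those who generate and assign the sequence, not those who treat.
- Dropout criteria: "Patients who fail or anticipate to fail in continuing at least seven sessions will be dropped from the study, too". The section does not say who judges this, by what criterion, or from what time.

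**The concern.** Requiring one session turns an all-randomised set into a modified one. That is a common and often harmless choice when nobody who can affect the start of treatment knows the arm, because non-starters are then lost in the same way from both arms. If someone who knows the arm can delay or withhold the first session, the omission can depend on both arm and prognosis. Participants of poor prognosis could then be missing from one arm only, in the analysis the trial treats as primary and under a label that tells readers no such selection is possible. With 27 per arm, a handful of people is enough to matter.

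The definition is stated in the article, so it is not a detail left to an unseen analysis plan.

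**Working it through.** **1. Is the start shielded from the arm?** Put the sections side by side. The practitioner either pierces the skin and elicits a needle sensation or applies a non-penetrating device, so the arm is evident to that person at the first session at the latest. To bring the right device, the practitioner must know it beforehand. Site practitioners also request the allocation. Nothing requires the decision to start to be made by someone unaware of the arm. The article never says outright that practitioners are unblinded; this is an inference, though a strong one.

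**2. Which removals alter the set?** Only those between allocation and the first session. Anyone removed after one session meets the definition and stays in, with LOCF. The primary outcome is measured at baseline and end, so a participant without an end measurement carries the baseline value, that is, zero change.

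**3. The plan's own figure.** Sample size section: 42 in total, 20 % dropout, 1:1.
- 42 / 2 = 21 per arm; 21 / (1 − 0.20) = 26.25, rounded up to 27; 2 × 27 = 54. This reproduces the plan.
- The step to 42 cannot be checked, because the EA change and the standard deviation (SD) are not given.
- One participant is 1/27 = 3.7% of an arm.

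**4. Dilution.** Assumptions, not in the article: treated EA participants change by −0.15 in the PVR ratio, EA non-starters by 0. With k non-starters, the mean of all 27 is −0.15 × (27 − k)/27.

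| k | All 27 | Non-starters left out | Difference | Share (k/27) |
|---|---|---|---|---|
| 1 | −0.144 | −0.150 | 0.006 | 3.7% |
| 2 | −0.139 | −0.150 | 0.011 | 7.4% |
| 3 | −0.133 | −0.150 | 0.017 | 11.1% |

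The share is k/27 whatever treated change is assumed. It is a share of the between-arm effect only if sham participants do not change. It contains no selection on prognosis: the same shift appears if non-starting is purely random.

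**5. Selection.** Assumptions, not in the article: no true effect, 27 randomised per arm, two-sided t-test at 0.05, 40,000 simulated trials per setting. The m EA participants of worst prognosis leave before the first session; ρ is the correlation of prognosis with outcome. The table gives the probability of a significant result favouring EA (nominal 0.025).

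| ρ | m = 1 | m = 2 | m = 3 |
|---|---|---|---|
| 0.3 | 0.030 | 0.035 | 0.042 |
| 0.5 | 0.035 | 0.045 | 0.056 |
| 0.7 | 0.040 | 0.060 | 0.077 |

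The mean bias runs from 0.02 SD (ρ = 0.3, m = 1) to 0.14 SD (ρ = 0.7, m = 3). If non-starting is unrelated to arm and prognosis, the bias is zero.

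**The case against.** The strongest reply is that the route to bias is narrow. The dropout sentence has the patient as its subject, and patients are blinded. Its verb concerns continuing, which most naturally means after treatment has begun. The article gives no sign of a long gap between allocation and first session, and the Exclusion criteria already keep out people who fear acupuncture, one plausible reason for not starting. The set is openly defined, so a careful reader can see what it is.

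Most of this stands. A reader might infer that the dropout rule lets site staff remove participants from the primary result at will. The text does not support that: staff judgement before the first session is one possible reading, which the wording neither states nor excludes, and later removals leave the set unchanged. A reader might also infer that the primary comparison has lost the protection of randomisation. That goes too far as well: it would need an unblinded practitioner to withhold first sessions selectively by arm and prognosis, and nothing in the article describes this.

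What the reply does not remove is the main point. The definition leaves out non-starters, the people who give the first session can know the arm, and no provision closes the gap. Open definition does not cure the label, which promises more than the set delivers.

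**Conclusion.** The point holds as an avoidable risk of bias in the primary analysis set, of unknown and possibly zero size. It rests on two things: the stated one-session requirement, and the inference from Blinding, Interventions and Randomization that practitioners know the arm by the first session. It does not depend on the dropout rule, which adds to the risk only if it is read as applying before treatment.

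Neither calculation estimates what will happen in this trial. The 3.7 to 11.1% figures show dilution when one to three EA non-starters have zero change. The error rates of 0.030 to 0.077 are a worst case of fully selective omission from one arm. They show that small numbers could matter at this sample size. The change is worth making because it is cheap, not because harm has been shown.

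**What to change.** - Define the primary set as all randomised participants, analysed in the allocated arm, whether or not a session was given.
- Keep the set with at least one session for safety and as a sensitivity analysis labelled modified ITT.
- Report non-starters by arm, with reasons.
- Reconcile Dropout criteria with Data analysis, so that participants who do not start or who stop sessions still have the end-point PVR sought on the scheduled day. The Primary outcome section times that measurement from the last session, so a scheduled day has to be stated for those who had none.

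Cost: a few sentences across these sections, and the effort of measuring people who are not being treated. The recruitment target stays at 54. Untreated participants dilute the estimate slightly. Any non-starter who is not measured would enter under LOCF with the baseline value, an imputed zero change rather than an observed outcome, so the benefit depends on obtaining the measurement.

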**Methods/design:**

A multicenter, blinded, randomized controlled trial will be conducted in three hospitals in the Republic of Korea. We are recruiting 54 stroke survivors (aged >19 years), who were diagnosed with urinary retention based on the results of two consecutive post-void residual (PVR) tests, and dividing them randomly into two arms: the EA and Park-sham control groups.

They will receive ten sessions of EA or sham treatment for 2 weeks. The participants will be blinded with non-penetrating needles and fake sounds of EA stimulators. The daily PVR ratio will be primarily measured at baseline and at the end of the study to statistically test the effectiveness of EA for poststroke urinary retention. Then, the Korean version of the Qualiveen Questionnaire, the Korean version of the International Prostate Symptom Score, and the blinding index will be assessed. After each EA session or sham EA, adverse events will be reported to evaluate the safety of EA.

Results will be analyzed by using the independent *t*-test or Mann-Whitney *U* test, based on both intention-to-treat and per-protocol principles.

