### Primary outcome

To evaluate the effectiveness of EA treatment over the sham device for poststroke UR, we will primarily assess the change in daily PVR urine ratios between the baseline and end point of the last session. The daily PVR ratio is computed by dividing the daily PVR urine volume by the daily PVR urine volume plus spontaneous voiding volume. The daily PVR urine volume for 24 hours will be examined with ultrasonography scanning. If the PVR urine volume is more than 100 mL, the residual will be removed through intermittent cauterization before the scanning. When spontaneous urination is impossible, a 24-hour weight change in diaper will be measured for the self-voiding volume.

If the urinary tract is infected at the end, the outcome assessor will measure the PVR urine volume on the third day of the last session after anti-UTI treatment for 48 hours. Otherwise, PVR urine volume will be measured on the next day of the last session.

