### Secondary outcome

Because UTI might affect the urine residuals [18, 19], the patients in both groups will undergo urinalysis to determine whether UTI exists before PVR urine volume evaluation at the end point. UTI is diagnosed when nitrite is detected by urinalysis and two of the following clinical symptoms exist: pyuria, lower abdominal pain, or hematuria [20]. The urinalysis retest is performed after 48 hours of antibiotics treatment.

We will also assess disease-specific QoL by using the Korean version of the Qualiveen Questionnaire (K-QQ). This is an assessment tool consisting of 30 items for patients with neurogenic bladder [21–24]. Each item, rated from 0 to 4 points, evaluates patients’ bladder problems, while the additive nine questions, rated from −2 to +2 points, are about patients’ general QoL status. The higher the absolute value of the total K-QQ score, the lower the QoL becomes. We will measure the K-QQ scores at baseline and at the end of the last session.

The Korean version of the International Prostate Symptom Score will be assessed at baseline and at the end point. This scale is generally used to evaluate general symptoms related to the lower urinary tract [25, 26]. The total score (0–35) is calculated by seven items of 0–5 points each, and the severity will be assessed as mild (0–7 points), moderate (8–19 points), or severe (20–35 points).

The frequencies of urination and urinary incontinence will also be reported. The patients will record them by urinary diary for 1 day before the first intervention and for another day after the last intervention. The mean change from posttreatment to pretreatment in the EA group will be compared with that in the sham group.

Finally, we will measure the blinding index (BI) for all of the participants at the end of the verum or the sham EA. The success or failure of the participants’ blinding will be assessed by using the validated scale [27]. The outcome assessor will ask the participants where they belong by selecting one of the following responses: “I think I belonged to the EA group,” “I think I belonged to the sham group,” or “I don’t know which group I belonged to.”

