### Sample size

Based on a previous study [2], the mean percentage change in PVR ratios in the EA and control groups were computed. We assumed an after-treatment PVR ratio of 0.65 in the control group, as it was not reported in the study. The null hypothesis was that the percentage changes in PVR ratios have no significant difference between the intervention and control groups. With a significance level of 0.05 and a statistical power of 0.8, the calculated sample size in total was 42 [28]. Considering a 20 % drop rate at a 1:1 allocation ratio, we will recruit 27 participants for each group.

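### With only baseline and end measurements, last observation carried forward scores each treated patient without an end value as exactly zero change, which shrinks or distorts the primary contrast

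*Protocol article*

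**What the plan says.** - **Outcome.** Under Primary outcome: "we will primarily assess the change in daily PVR urine ratios between the baseline and end point of the last session". The Abstract gives the times: "The daily PVR ratio will be primarily measured at baseline and at the end of the study". If there is no urinary tract infection, "Otherwise, PVR urine volume will be measured on the next day of the last session"; if there is one, measurement moves to the third day. No PVR ratio between baseline and end is described.
- **Secondary outcomes.** For the Qualiveen questionnaire, "We will measure the K-QQ scores at baseline and at the end of the last session". The prostate symptom score and the one-day diary follow the same two-point pattern.
- **Who leaves.** Besides unwilling patients, Dropout criteria states: "Patients who fail or anticipate to fail in continuing at least seven sessions will be dropped from the study, too".
- **Who is analysed.** Data analysis states: "The ITT analysis will include any participants who are randomly allocated and have at least one EA or sham session". This set is primary and the per-protocol set is subordinate.
- **Missing data.** The only rule given is "Missing values will be imputed by the last observation carried forward".
- **Sample size.** 42 patients in total give 80% power at the 0.05 level. After allowing for 20% dropout, "we will recruit 27 participants for each group".

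**The concern.** Carrying the last observation forward presupposes intermediate observations. Here there are none, so the rule becomes baseline carried forward, and the imputed change, absolute or percentage, is zero by construction. At the planned dropout rate this could affect about 11 of 54 patients (0.20 × 54 = 10.8).

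Two things follow. First, the sample size and the primary analysis treat the same patients in incompatible ways: one counts them as contributing nothing, the other as patients who did not change. Second, zeros pull each arm's mean towards no change in proportion to that arm's dropout. With equal dropout this dilutes the contrast. With unequal dropout and a change common to both arms, it creates a difference where none exists. The single primary comparison of the trial is affected.

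**Working it through.** **Inputs.** From Sample size: significance level 0.05 (taken as two-sided; the article does not say), power 0.80, 42 in total (21 per arm), 20% dropout, 27 per arm. The article gives no SD, no expected difference and no sham change. Changes are therefore expressed in SDs of the change, and the sham change is an assumption shown over a range.

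**The plan's own figure.** 21 / 0.8 = 26.25, rounded up to 27 per arm, 54 in total. This reproduces, and it treats dropouts as lost. The 42 itself cannot be derived without a difference and SD, so it is inverted: a two-sided t-test with 21 per arm and 80% power implies a standardised difference d = 0.886.

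**Model under the stated rule.** A share p of each arm has change 0; the rest have mean μ and SD 1, with dropout unrelated to outcome.
- Arm mean = (1 − p)μ
- Arm variance = (1 − p) + p(1 − p)μ²

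**Equal dropout, p = 0.2.** The expected contrast is 0.8 × 0.886 = 0.709, which is 80% of the full-follow-up contrast whatever the sham change. Each arm's variance is 0.8 + 0.16μ². With 27 per arm, SE = √[(sum of the two variances)/27], and power comes from the non-central t distribution on 52 degrees of freedom with non-centrality 0.709/SE:

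| Sham improvement (assumed) | Variance, sham | Variance, EA | SE | 0.709/SE | Power |
|---|---|---|---|---|---|
| 0 | 0.800 | 0.926 | 0.253 | 2.80 | 79% |
| 0.5 SD | 0.840 | 1.107 | 0.269 | 2.64 | 74% |
| 1 SD | 0.960 | 1.369 | 0.294 | 2.41 | 66% |

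**Comparison without the zeros.** About 0.8 × 27 = 21.6 observed per arm gives SE = √(2/21.6) = 0.304, an unbiased contrast of 0.886 and power of 81%. The SE ratio to the stated rule is 0.304/0.253 = 1.20 if sham does not change and 0.304/0.294, about 1.04, if sham improves by 1 SD.

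**No true effect.** With equal 20% dropout, simulated type I error of the t-test stays near 5% for a common improvement of 0, 0.5 or 1 SD. With 10% versus 30% dropout (an assumption), the spurious difference is 0.9μ − 0.7μ = 0.2μ. Simulated type I error is then about 7% for μ = 0.5 and 12% for μ = 1. It stays at 5% for μ = 0. The excess rejections favour the arm with fewer dropouts, because both arms are assumed to improve.

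**The case against.** Several stronger readings are tempting, and the article does not support them.

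- **Every dropout is scored as zero.** Patients with no session are outside the intention-to-treat set. The article also does not say that a withdrawn patient can never have an end measurement, although the dropout rule points that way.
- **The 80% power is lost.** If sham does not change, the loss is about one point, because the smaller contrast is nearly offset by the smaller variance. The Discussion describes the sham device as validated to be inactive, and Interventions bars other treatment that could affect retention. The 74% and 66% figures need a sham improvement that the article neither states nor rules out.
- **The test is anti-conservative.** Not at the planned dropout. The article gives one 20% rate and blinds participants, so the inflation needs both unequal dropout and a common change.
- **The arm with fewer dropouts always gains.** This holds only if both arms improve. With no common change there is no spurious difference, and if both arms worsen the direction reverses.
- **Early recovery after stroke makes zero change implausible.** The article gives only a two-year window since stroke and says nothing about recovery.

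It can also be argued that patients with fewer than seven sessions benefit less, so some dilution suits an intention-to-treat principle. That is fair as far as it goes, but zero is then an assumption about outcome that should be stated and tested; here it is a by-product of the visit schedule. The per-protocol analysis relies little on imputation, but it is subordinate and also excludes patients with urinary tract infection at the end.

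**Conclusion.** The point stands in this form: the rule the protocol fixes for its primary analysis assigns zero change to each treated patient without an end value, and this conflicts with how the sample size treats the same patients. At the planned 20% dropout in both arms, the contrast is expected to be 80% of its full-follow-up size, provided dropout is unrelated to outcome. That result needs no SD or sham change.

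The consequences for power (79% down to 66%) and for type I error (5% up to 12%) are conditional. They rest on assumed sham changes of 0 to 1 SD, an assumed 10% versus 30% split and a two-sided test, and should be read as a range. This is a method the article states, so it is not a detail left to a later analysis plan.

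**What to change.** In Data analysis, replace last observation carried forward as the primary method by one valid under a stated missing-at-random assumption. Two options:
- multiple imputation by arm from baseline ratio and site; or
- ANCOVA on the observed end values, given baseline and site.

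Sessions received should not be relied on as an imputation predictor. The seven-session dropout rule leaves little overlap between dropouts and completers, so the model would extrapolate.

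Obtain the end measurement where possible from patients who stop sessions early but still consent to assessment, since observed values are better than any imputation. Keep baseline carried forward and a delta-shifted imputation as sensitivity analyses. Apply the same approach to the questionnaire and diary outcomes.

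**Cost.** The analysis change is wording only and needs no extra patients; the added end measurements need some follow-up effort. Before any gain from baseline adjustment, the standard error is about 4% to 20% larger than under the present rule. The primary result will rest on the missing-at-random assumption, which the sensitivity analyses are there to test.

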### Randomization

Random sequences were generated separately in each site with the R package (R Foundation for Statistical Computing, Vienna, Austria, https://www.r-project.org) to allocate participants into either the EA or sham group. The allocation ratio was 1:1. From each center, at least 14 participants will be recruited, and the last 12 persons will be competitively enrolled among all the three sites. Only the delegated sub-investigators can access the security electronic file of the randomization table and assign the participants. Practitioners from each site will call or send a message to the sub-investigators in order to allocate the participants in their own hospitals. After assignments are completed, a sub-investigator from the primary site, Kyung Hee University Korean Medicine Hospital, will allocate the 12 participants from the three sites to the last participant. The investigators, who will generate the random number and assignments, will be blinded to the arm where each participant will be allocated.

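### The primary comparison is an unadjusted t-test or Mann-Whitney test picked by a normality check. It is valid, but it can lose precision and leaves the effect measure to the data.

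*Protocol article*

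**What the plan says.** Four sections of the protocol article bear on this.

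- **Data analysis** sets one rule for all continuous outcomes: "Continuous variables will be tested by the independent *t*-test if normality is obtained". If not, "Otherwise, the Mann-Whitney *U* test will be implemented". No covariate or site term is named, and the abstract gives the same two tests.
- **Primary outcome**: "we will primarily assess the change in daily PVR urine ratios between the baseline and end point of the last session". Baseline is therefore measured, and it is used by subtraction.
- **Randomization**: "Random sequences were generated separately in each site with the R package", at 1:1. Each of three sites recruits at least 14, and the last 12 places are filled competitively. No blocking is stated.
- **Sample size**: "The null hypothesis was that the percentage changes in PVR ratios have no significant difference between the intervention and control groups". So the sizing uses percentage change, while the Primary outcome section speaks of change in the ratio. Then: "With a significance level of 0.05 and a statistical power of 0.8, the calculated sample size in total was 42".

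**The concern.** Three features of the stated rule deserve attention.

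1. A raw change score fixes the coefficient on baseline at 1. Unless that happens to be the best coefficient, a model that estimates it has a smaller residual variance. Eligibility is an absolute residual above 100 mL, with no limit on the ratio, so baseline ratios may vary widely. In 54 patients a chance imbalance at baseline is possible, and the change score over-corrects for it whenever the regression of end value on baseline has a slope below 1.
2. If the site-wise lists kept the arms balanced within site, between-site variation does not contribute to the error of the treatment difference. An unadjusted test still counts it.
3. The normality check makes the effect measure depend on the data. The result is either a difference in means or a comparison of ranks, and which one is unknown until the data are seen.

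At stake are precision that the trial could have from variables it already collects, and a primary effect measure fixed in advance. The trial is sized at 80% power and has little margin: "We assumed an after-treatment PVR ratio of 0.65 in the control group, as it was not reported in the study".

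**Working it through.** **Inputs from the article.** Alpha 0.05 (sidedness not stated, taken as two-sided), power 0.80, 42 evaluable patients (21 per arm), 20% dropout, 1:1 allocation, 54 recruited, three sites.

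**Not given, so assumed.** The treatment difference and SD; the baseline-to-end correlation rho; the ratio k of baseline SD to end SD; the share of the variance of change that lies between sites; whether allocation was blocked within site.

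**1. The plan's own figures.** Dropout: 21 / 0.8 = 26.25, rounded up to 27 per arm, or 54. This reproduces. The 42 cannot be rebuilt without a difference and an SD. Back-solving the standardised effect d from 21 per arm gives:

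- normal approximation: d = (1.960 + 0.842) × sqrt(2/21) = 0.865;
- noncentral t, 40 degrees of freedom: d = 0.886, used below.

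**2. Baseline as covariate, equal SD s at both visits.**

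- Var(change) = 2s²(1 − rho)
- Var(ANCOVA) = s²(1 − rho²)
- Ratio = (1 + rho)/2

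Power at 21 per arm follows from d / sqrt(ratio):

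| rho | variance ratio | d / sqrt(ratio) | power | n per arm for 80% |
|---|---|---|---|---|
| change score | 1 | 0.886 | 80% | 21 |
| 0.3 | 0.65 | 1.099 | 93% | 14 |
| 0.5 | 0.75 | 1.023 | 90% | 16 |
| 0.7 | 0.85 | 0.961 | 86% | 18 |
| 0.9 | 0.95 | 0.909 | 82% | 20 |

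The last column uses the normal approximation. Adding two site terms as well (37 degrees of freedom instead of 39) costs about 0.1 percentage point of power.

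**3. Unequal SDs.** The ratio becomes (1 − rho²) / (1 + k² − 2k·rho). With k = 0.7:

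- rho 0.3: 0.91 / 1.07 = 0.85, a 15% cut in variance;
- rho 0.5: 0.75 / 0.79 = 0.95, a 5% cut;
- rho 0.7: 0.51 / 0.51 = 1.00, no cut.

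With k = 1.3 and rho 0.5 it is 0.75 / 1.39 = 0.54, a 46% cut. The gain therefore depends heavily on k.

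**4. Site.** Suppose arms are exactly balanced within site and a share f of the variance of change lies between sites. The true variance of the treatment difference is then (1 − f) times what the unadjusted test assumes. Type I error is approximately 2 × [1 − Φ(1.96 / sqrt(1 − f))]:

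- f = 0.1: 0.039
- f = 0.2: 0.028

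If site effects are instead drawn at random, the loss is milder. A simulation with three sites of 14, rho 0.5, 6,000 null runs (Monte Carlo standard error about 0.003) and 4,000 runs under d = 0.886 gave:

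| setting | type I error, unadjusted t | power, unadjusted t | power, ANCOVA with site |
|---|---|---|---|
| no site effect, balanced | 0.044 | 0.81 | 0.89 |
| site share 0.1, balanced | 0.041 | 0.77 | 0.88 |
| site share 0.2, balanced | 0.038 | 0.74 | 0.89 |
| site share 0.2, simple randomisation | 0.050 | 0.72 | 0.85 |

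**5. The normality switch.** In the same runs the switched rule had type I error between 0.039 and 0.051, so no inflation. With skewed data its power was 0.95, against 0.82 for the plain t-test and 0.90 for ANCOVA.

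**The case against.** The strongest reply is that nothing here is invalid. Under randomisation a change-score comparison is unbiased and holds its error rate. That stands, and it rules out three stronger readings.

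- **That baseline is ignored.** It is not: the primary outcome is a change, so baseline enters by subtraction. What is missing is its use as a covariate.
- **That the standard error is wrong.** This needs forced balance within site, and the article states no blocking. It also needs sites to differ in change, since stable site differences in the ratio cancel on subtraction. When both hold, the error is in the conservative direction. With simple randomisation within site the standard error is about right.
- **That the normality check inflates false positives.** The simulations show no such inflation. The PVR ratio is bounded by 0 and 1, so skew is plausible, and a rank test may then beat ANCOVA.

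It is also fair that the power figures rest on rho and k, which the article does not give. They further carry an effect size back-solved from a percentage-change calculation over to absolute change in the ratio. They show a possible range, not an estimate of what this trial loses.

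A last reply is that a separate analysis plan may hold the model. But the article does not leave the test open. It names it, in both the abstract and the Data analysis section.

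**Conclusion.** The concern holds as a matter of efficiency and of an effect measure that is not fixed in advance. It is not a matter of validity.

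- **Baseline.** With equal SDs at both visits, ANCOVA would add about 2 to 13 points of power at 21 per arm for rho from 0.9 to 0.3 (10 points at 0.5). The gain can vanish if the baseline SD is below the end SD, and is larger if it is above.
- **Site.** If arms are balanced within site and 10% to 20% of the variance of change lies between sites, type I error is about 0.03 to 0.045. Otherwise it is about nominal. False positives are not inflated in either case.
- **Effect measure.** The data choose between a mean difference and a rank comparison. The mismatch between change in the ratio and percentage change adds a second ambiguity.

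This is a free or cheap improvement that is worth making. It does not have to be made for the trial to be interpretable.

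**What to change.** Pre-specify one primary analysis: ANCOVA of the end-of-study daily PVR ratio on arm, baseline daily PVR ratio and site (three levels), reporting the adjusted mean difference with its 95% CI. Use the same model for the Qualiveen and Prostate Symptom scores.

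Drop the normality-triggered switch. In its place, specify a fixed rank-based or permutation sensitivity analysis, stratified by site and reported whatever the distribution looks like.

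State that this model on the ratio is the primary endpoint analysis. That settles whether the trial tests change in the ratio (Primary outcome) or percentage change (Sample size), and the sample-size paragraph should be brought into line.

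The cost is analysis wording and about three degrees of freedom. All the variables are already collected, and no patient, visit or procedure changes. The one real downside is that, if the ratio is strongly skewed, a rank test may have more power than ANCOVA. The fixed sensitivity analysis shows whether the conclusion depends on that choice, but it does not restore the lost power to the primary test.
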